#### **4.2.2.2 CANTAB cognitive battery test**

Patients' cognitive functions will be assessed by CANTAB computerized cognitive tests (Cambridge cognition, England) [52]. The CANTAB is a semiautomated test battery which can be administered on a laptop PC and more recently has been modified for administration on a handheld tablet. The current release of CANTAB Eclipse comprises 25 tests designed to assess components of cognitive function which fall into 7 broad groups of tests: visual memory, executive function, working memory and planning, attention, semantic/verbal memory, decision making and response control, social cognition, and screening/familiarization.

CANTAB tests evaluate various aspects of brain functions and include: Memory tests (paired associated learning, delayed matching to sample, graded naming test, pattern recognition memory, spatial recognition memory, verbal recognition memory, spatial span, spatial working memory), Attention tests (reaction time, rapid visual information processing, choice reaction time, simple reaction time, match to sample visual search, attention switching task), Executive Function tests (one touch stockings of Cambridge, attention switching test, intra-extra dimensional set shift, spatial span, spatial working memory, stop signal task), Decision making tests (Cambridge gambling task, affective Go-No-Go, information sampling task). Cognitive index scores will be computed from normalized outcome parameters for these tests for memory, executive function,

|                                                     |                                                        |                                        |
|-----------------------------------------------------|--------------------------------------------------------|----------------------------------------|
| Investigational Product
Hyperbaric chamber       | Short Title:                                           | Protocol No.
058-17-ASF             |
| Phase:
Investigator Initiated Phase
III study | Hyperbaric Oxygen Therapy for Fibromyalgia
Syndrome | Version, Date
Ver.4.0, 10 OCT, 2017 |

attention, decision making, social cognition [53, 54]. A global cognitive score will be computed as the average of all index scores for each individual. Notably, the patients will be given three different test versions of the CANTAB test battery at baseline, 3 months control period and after HBOT, to allow repeated administrations with minimal learning effect. Test-retest reliability for those versions will be evaluated and found high, with no significant learning effect [55].

### ***4.2.3 Brain imaging***

Brain imaging will include 2 type of imaging: perfusion MRI+DTI including resting state functional MRI and Brain SPECT.

#### ***4.2.3.1 Perfusion MRI+DTI***

The MRI protocol includes the following sequences: Axial T1, T2, FLAIR, Axial Diffusion weighted, Axial T1-PostGad, DSC, DCE, DTI, FLAIR,T1, T2 and SWI. MRI scans sequences parameters:

- **DSC:** 50 T2\*-weighted gradient-echo echo planar imaging (EPI) volumes will be acquired, 2 repetitions before a bolus injection of Gadolinium-DTPA (Gd-DTPA), 48 repetitions after injection of Gd-DTPA. Sequence parameters: TR=2,300 ms, TE= 40ms, flip angle = 30°, voxel size = 1.8 x1.8, Matrix = 128x128, No. of slices = 25, Slice thickness = 3.9 mm.
- **DCE:** three T1 weighted Fast Low Angle SHot (FLASH) volumes will be acquired with different flip angles (2, 7 and 15 degrees) followed by 70 dynamic T1 weighted FLASH volumes with flip angle of 15 degrees after bolus injection of Gd-DTPA. Sequence parameters: before injection: TR=4.09, after injection - TR=4.86 ms, TE= 1.76 ms, Voxel size = 1.5x1.5, Matrix = 192X192, No. of slices = 26, Slice thickness = 3.5mm.
- **DTI:** 30 diffusion weighted images will be scanned with different gradient directions (b=1000) and one volume without diffusion weighting, with the following parameters: TR=10,300 ms, TE=89 ms, Voxel size = 1.8X1.8, Matrix = 128 X 128, No. of slices = 63, Slice thickness = 2.2mm

|                                                     |                                                        |                                        |
|-----------------------------------------------------|--------------------------------------------------------|----------------------------------------|
| Investigational Product
Hyperbaric chamber       | Short Title:                                           | Protocol No.
058-17-ASF             |
| Phase:
Investigator Initiated Phase
III study | Hyperbaric Oxygen Therapy for Fibromyalgia
Syndrome | Version, Date
Ver.4.0, 10 OCT, 2017 |

- ***Resting state fMRI (rsfMRI\ R-fMRI)***: a method of functional brain imaging that can be used to evaluate regional interactions that occur when a subject is not performing an explicit task. This resting brain activity is observed through changes in blood flow in the brain which creates what is referred to as a blood-oxygen-level dependent (BOLD) signal that can be measured using fMRI.

#### ***4.2.3.2 Brain SPECT***

Brain single photon emission computed tomography (SPECT) will be conducted using 925–1,110 MBq (25–30 mCi) of technetium-99m-methyl-cysteinate-dimer (Tc-99m-ECD) at 40–60min post-injection using a dual detector gamma camera (Symbia T, Siemens Medical Systems) equipped with high resolution collimators. Data will be acquired in 3-degree steps and reconstructed iteratively with Chang method ( $\mu=0.12/\text{cm}$ ) attenuation correction.

Both pretreatment and post-treatment SPECT images will be normalized to the median maximal brain activity in the entire brain and will be then reoriented into Talairach space using Oasis Neurology - NeuroGam application (Segami Corporation, Columbia, MD, USA) to identify Brodmann cortical areas and to compute the mean perfusion in each Brodmann area (BA).

#### ***4.2.4 Brain Network Activation (BNA™) Analysis***

BNA™ Analysis System is a software only device that utilizes advanced algorithms to analyze the brain network activity of the brain from the recorded EEG data (AMAR: 27860001). The BNA™ Analysis system provides both qualitative network maps of the activity as well as quantitative scores that can be used as a neuromarker for disease. Event Related Potentials (ERPs), which are temporal reflections of the neural mass electrical activity of cells in specific regions of the brain that occur in response to stimuli, may offer such a method, as they provide both a noninvasive and portable measure of brain function. The ERPs provide excellent temporal information, but spatial resolution for ERPs has traditionally been limited. However, by using high-density electroencephalograph (EEG) recording spatial resolution for ERPs is improved

|                                                     |                                                        |                                        |
|-----------------------------------------------------|--------------------------------------------------------|----------------------------------------|
| Investigational Product
Hyperbaric chamber       | Short Title:                                           | Protocol No.
058-17-ASF             |
| Phase:
Investigator Initiated Phase
III study | Hyperbaric Oxygen Therapy for Fibromyalgia
Syndrome | Version, Date
Ver.4.0, 10 OCT, 2017 |

significantly [56-59]. The paradigm for the current study will combine neurophysiological knowledge with mathematical signal processing and pattern recognition methods (BNA™) to temporally and spatially map brain function, connectivity and synchronization.

The following parameters will be evaluate by BNA™ technology:

- **Visual GO/NO-GO** - The Go/No-Go paradigm is among the most well-established tests of response inhibition to perceptual stimuli. The task involves sensory processing, motor activity (a response) and response inhibition. In this task, subjects see a series of alphabetical letters and are required to react according to the letters. Letters are presented every 2 seconds on average. 80% of the stimuli are the letters B, C, D, E, F or G providing the Go cues ("Sensory"), to which subjects are asked to respond as quickly as possible ("Motor"), and 20% are an "X" providing the No-Go cue ("Response inhibition"), that require subjects to inhibit their response. The stimuli are presented on the center of a black background monitor for 150 ms and are located between two vertical white lines which remains constant throughout the task. The inter stimulus interval varies randomly between 1000 ms and 2600 ms with steps of 250 ms. The total number of trials is 400. Task duration is ~14 minutes.
- **Auditory Oddball** - The auditory oddball task is a classic EEG paradigm that has been studied extensively and used in a variety of neurological patient populations. The task involves executive functions, attention and memory processes. In this task, subjects hear a series of auditory tones and are required to react according to the tones. Tones are presented once every 1.5 seconds on average. A total of 80% of the sounds ("Sensory") are 2000 Hz tones. A total of 10% of the sounds ("Memory") are 1000 Hz tones to which participants respond by pressing a button. The remaining 10% of sounds ("Attention") are complex sounds.
- **Sensory Evoked Potential** - Contact heat stimuli were delivered to the right, dominant proximal volar forearm using a round thermode of 572.5 mm^2 (PATHWAY, Medoc Ltd., Ramat-Yishai, Israel) in four-block heat stimulation sessions to produce Contact heat evoked potential (CHEPs). Each CHEPs stimulus

|                                                     |                                                        |                                        |
|-----------------------------------------------------|--------------------------------------------------------|----------------------------------------|
| Investigational Product
Hyperbaric chamber       | Short Title:                                           | Protocol No.
058-17-ASF             |
| Phase:
Investigator Initiated Phase
III study | Hyperbaric Oxygen Therapy for Fibromyalgia
Syndrome | Version, Date
Ver.4.0, 10 OCT, 2017 |

trial began with the thermode applied to the skin, followed by the triggering of the heat stimulus, and ended with a beep, which prompted subjects' to rate the pain produced by the heat stimulus. This thermode application was repeated in a clockwise manner on the designated area of the forearm. On Visit 1, subjects underwent a temperature-determination protocol, in which they received three different heat stimuli of the same temperature, ranging from 38°C to 52°C. Subjects were instructed to rate each stimulus on a numeric rating scale (NRS), where 0 indicated the absence of pain and 10 indicated the worst imaginable pain. The two temperatures which subjects rated as 3 and 6 on the NRS were chosen as the low and high-temperature, respectively, used during proceeding Pre and Post HD-tDCS EEG recordings. The first two blocks of heat stimuli used the low-temperature determined (NRS rating of 3) for each individual subject and were separated by a 5 minute interval. The following two blocks of heat stimuli used the high-temperature determined (NRS rating of 6) for each individual subject and were also separated by a 5-minute break. The low and high-temperature blocks were further separated by a 15-minute interval between them. There were 20 stimuli (trials) per block and the inter-stimulus interval ranged from 8 to 13 sec.

- **Resting States** - EEG will be recorded at rest (no cognitive task), several minutes with eyes open and several minutes with eyes closed (between 2 and 5 min). The aim of the resting EEG recording is to extract patterns of the DMN. The DMN is a network comprising many brain regions which show in fMRI studies reduced activation during task execution. Recently, the DMN has been studied also in EEG signals (Laufs et al. 2003).

#### ***4.2.5 Pain threshold and conditioned pain modulation (CPM)***

Pressure pain threshold (PPT) will be assessed using a handheld computerized pressure algometer with a circular 1 cm^2 probe (AlgoMed, Medoc LTD, Israel). PPTs will be measured three times at the upper trapezius muscle. The baseline pressure applied will be 0 kPa, with incremental increases of 30 kPa per second, up to a maximal pressure of 1000 kPa. The participant will be instructed to report when the sensation changed from

|                                                     |                                                        |                                        |
|-----------------------------------------------------|--------------------------------------------------------|----------------------------------------|
| Investigational Product
Hyperbaric chamber       | Short Title:                                           | Protocol No.
058-17-ASF             |
| Phase:
Investigator Initiated Phase
III study | Hyperbaric Oxygen Therapy for Fibromyalgia
Syndrome | Version, Date
Ver.4.0, 10 OCT, 2017 |

pressure to pain, at which point the probe will be removed. The average of the second and third measurements will be used in further analyses. Decreased inhibitory conditioned pain modulation (CPM) effectiveness has been observed in FMS patients (*de Souza JB et al. The Clinical journal of pain 2009; Julien N et al. 2005; Kosek E et al. 1997; Lautenbacher S, et al. 1997; Paul-Savoie E et al. 2012*). For evaluating CPM, The PPT test will be repeated during immersion of non-dominant hand to 10 degrees cold water. The CPM is the difference in mean pain intensity between the tests. Thus, effective pain inhibitory mechanisms are represented by higher (positive) values (*Philippe Chalaye et al. 2013*).

During the pain intensity evaluation (CPM efficacy) brain cortical activity will be continuously monitored using the EEG -DELPHI system (Amar: 570406) evaluating the cortical manifestation of the chronic pain and its correlation with the evaluated CPM efficiency.

#### **4.2.5.1 Pain evaluations**

Participants evaluated pain intensity with a computerized numeric pain rating scale (CNPRS) ranging from 0 (no pain) to 10 (most intense pain tolerable).

- **Heat pain threshold and heat pain tolerance** - Heat pain threshold is determined as the minimum temperature causing pain and heat pain tolerance is established as the highest tolerable temperature.

Thermal pain is induced with thermal electrode (thermode). Thermode temperature will initially be set at 32.0°C and gradually increase at a rate of 0.3°C/sec. Participants will be instructed to report when the sensation produced by the thermode changed from heat sensation to pain (heat pain threshold) and when the pain became unbearable (heat pain tolerance). This procedure will be conducted twice for every subject and the mean of the two trials will be calculated. The thermode will be placed on adjacent areas of the forearm for every trial to avoid primary skin hyperalgesia.

- **Heat test-stimulus (HTS)** - Following heat pain thresholds assessments, the thermode will be applied on the left forearm for 120 seconds at constant temperature. The temperature will be individually adapted to induce a mean pain intensity of 60/100 based on heat pain threshold and tolerance values using the following

|                                                     |                                                        |                                        |
|-----------------------------------------------------|--------------------------------------------------------|----------------------------------------|
| Investigational Product
Hyperbaric chamber       | Short Title:                                           | Protocol No.
058-17-ASF             |
| Phase:
Investigator Initiated Phase
III study | Hyperbaric Oxygen Therapy for Fibromyalgia
Syndrome | Version, Date
Ver.4.0, 10 OCT, 2017 |

formula: Heat pain threshold + ((heat pain tolerance - heat pain threshold)/2) (*Chalaye P et al. 2013*). Participant's pain intensity will be evaluated by CNPRS. If the pain intensity produced by this temperature will not induce an average pain of 60/100, the temperature will be adjusted accordingly. The 120-second HTS will be done before and after the CPT using the same thermode temperature. The thermode will be placed on adjacent areas of the forearm for every HTS trial to avoid primary skin hyperalgesia.

- **Cold Pressor Test (CPT)** - Participants immerse their dominant arm (up to the elbow) in circulating cold (12°C) water for 2 minutes. Participants will be instructed not to move or contract their arm during the immersion. Pain intensity ratings will be provided with the CNPRS automatically every 20 seconds during the entire 2-minute immersion period.

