### 3. Methods

#### 3.1 Study population

The study will include 70 fibromyalgia patients in whom physical trauma, such as mTBI, could be considered as the trigger for FMS. Each participant will be examined at the time of recruitment and a diagnosis of FMS will be verified, based on the updated 2016 diagnostic criteria [40]. These criteria are based on the use of the widespread pain index (WPI) and the Symptom severity Score (SSS).

Exclusion criteria will include the presence of systemic inflammatory disorders including inflammatory rheumatological and autoimmune disorders. Patients suffering from active malignancy, chronic ongoing infection and major psychiatric disorders (excluding anxiety) will be excluded. Patients currently or previously treated with Duloxetine (Cymbalta) or Pregabalin (Lyrica) will also be excluded.

In the current study we will recruit patients not currently being treated with medications specific for FMS, including SSRI, SNRI, gabapentanoids and tricyclics, opioids and medical cannabis. Patients who are on such treatment will be required to discontinue treatment 2 weeks before recruitment.

In addition, patients who have one of the following criteria will also be excluded: Patients will be excluded if they will have one of the following criteria: had been treated with HBOT for any other reason prior to their inclusion; Chest pathology incompatible with pressure changes (including active asthma); Inner ear disease; Claustrophobia; Inability to perform awake brain MRI test; Previous neurologic conditions (eg. Epilepsy, neuromuscular diseases, metabolic diseases, etc.); Brain tumors; Skull base fractures; Active malignancy; s/p neurosurgery that included: ventricular drainage, subdural hematomas drainage, epidural hematomas drainage, intracerebral hemorrhage evacuation. Depressed fracture surgery, (Patients suffering from Encephalomalacia per MRI imaging will not be excluded). Inability to provide informed consent.

|                                                     |                                                        |                                        |
|-----------------------------------------------------|--------------------------------------------------------|----------------------------------------|
| Investigational Product
Hyperbaric chamber       | Short Title:                                           | Protocol No.
058-17-ASF             |

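### In left-handed patients the protocol puts the heat test and the cold immersion on the same forearm, so the second heat rating may mix local cooling with central pain modulation

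*Protocol*

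**What the plan says.** Protocol Section 4.2.5.1 describes a heat test stimulus (HTS) and a cold pressor test (CPT).

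- Heat site: "the thermode will be applied on the left forearm for 120 seconds at constant temperature".
- Order: "The 120-second HTS will be done before and after the CPT using the same thermode temperature".
- Skin site between heat trials: "The thermode will be placed on adjacent areas of the forearm for every HTS trial to avoid primary skin hyperalgesia".
- Cold site: "Participants immerse their dominant arm (up to the elbow) in circulating cold (12°C) water for 2 minutes".

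The parent Section 4.2.5 defines the outcome, "The CPM is the difference in mean pain intensity between the tests", and says that higher positive values represent effective inhibition. It also describes another cold procedure: "For evaluating CPM, The PPT test will be repeated during immersion of non-dominant hand to 10 degrees cold water". There the pressure threshold is measured at the upper trapezius.

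Section 3.1 describes the population, "The study will include 70 fibromyalgia patients in whom physical trauma, such as mTBI, could be considered as the trigger for FMS", and lists its exclusions. Handedness is not among them. No section gives an alternative arm for left-handed patients, or an interval or re-warming step between the CPT and the second HTS.

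**The concern.** One site is fixed by side and the other by dominance. Nothing ties them together except the unstated assumption that every patient is right-handed. The heat test holds one individually calibrated thermode temperature constant before and after the cold, so that a change in rating can be attributed to modulation by the cold stimulus. That logic needs the tested skin to be otherwise unchanged. If the tested forearm has itself been in cold water, a lower second rating could come from local cooling, from central inhibition, or from both, and the data cannot separate them.

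On the scale in Section 4.2.5, cooling that lowers the second rating would be scored as better inhibition. Section 1.1 presents reduced conditioned pain modulation (CPM) as evidence for central sensitization, Section 2 makes mechanism an objective, and Section 4.2.5 plans to relate CPM efficiency to EEG. The measure therefore carries interpretive weight although it is secondary.

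**Working it through.** **1. Arm assignment, following Section 4.2.5.1 to the letter**

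| Patient | Heat test | Immersed to the elbow | Same forearm? |
|---|---|---|---|
| Right-handed | left forearm | right arm | no |
| Left-handed | left forearm | left arm | yes |

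Moving the thermode to neighbouring skin does not separate the sites in a left-handed patient, because immersion to the elbow covers the whole forearm. The stated purpose of that rule is to avoid hyperalgesia, not cooling.

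**2. Number of patients**

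The protocol gives no left-handed share, so 5%, 10% and 15% are assumptions. With 70 patients (Section 3.1):

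- 70 × 0.05 = 3.5
- 70 × 0.10 = 7
- 70 × 0.15 = 10.5

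That is about 4 to 10 patients. The chance of at least one left-handed patient is 1 − (1 − p)^70. At p = 0.05 this is 1 − 0.95^70 = 0.97, and it is higher at 10% and 15%.

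**3. Where the error goes**

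Write the measure as first heat rating minus second, so that positive means inhibition. Let m be true modulation and c the contribution of local cooling. The size of c is unknown; the protocol gives nothing from which to estimate it.

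- Right-handed patient: measure = m.
- Left-handed patient: measure = m + c.
- Mean at a single visit: shifted by p × c, that is 0.05c, 0.10c or 0.15c.
- Between-patient variance at a single visit (c the same in all left-handed patients and unrelated to m): increased by p(1 − p)c². This is 0.0475c², 0.09c² or 0.1275c². It bears on correlations with EEG.
- Change between visits in a left-handed patient: (m₂ + c₂) − (m₁ + c₁) = (m₂ − m₁) + (c₂ − c₁). If c is stable within a patient it cancels. If it varies from visit to visit, the remainder is noise.

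**4. Imbalance between arms**

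Randomization is 1:1 without stratification (Section 5.4). Treating the arms as two independent binomials of 35, the probability that they differ by 3 or more left-handed patients is 0.16, 0.31 and 0.40 at 5%, 10% and 15%. A difference of 3 shifts a single-visit contrast by (3/35)c = 0.086c. By step 3 it does not shift a contrast of changes if c is stable.

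**5. The plan's own figures**

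No stated figure depends on this point. The sample size in Section 6.1.2.1 reproduces: a difference of 30 with SD 40 gives 28.9 per arm by t-test, so 29 per arm and 58 in total; 58/0.85 = 68.2, so 69, or 70 for equal arms.

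**The case against.** The strongest case on the other side has five parts.

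- **The sequence is never labelled CPM.** The procedure that the protocol expressly names for CPM is the pressure test at the trapezius in Section 4.2.5, where the tested site is never immersed. This stands as a limit. However, the heat–cold–heat sequence sits under the CPM heading, and a difference in pain intensity fits heat ratings better than a pressure threshold. The overlap affects that sequence whatever it is called.
- **Recent cooling is inferred.** No interval between the CPT and the second HTS is stated, and nothing shows how long cooling persists under a heated thermode. This stands. A reader might conclude that every left-handed patient's reading is invalid; the text supports only that it may be confounded.
- **Treatment effects are naturally read as within-patient change.** Section 2 describes evaluation before and after treatment, and handedness is fixed, so a stable offset largely cancels. This stands. A reader might take the 31% chance of imbalance as a chance of a biased treatment comparison. It is not: it counts patients, chance imbalance in a baseline trait is ordinary under randomization, and no treatment-by-cooling interaction is shown.
- **The immersed limb is itself unsettled.** Section 4.2.5 uses the non-dominant hand at 10 degrees; Section 4.2.5.1 uses the dominant arm at 12°C. This stands. The finding that right-handed patients escape the overlap holds only for the text of Section 4.2.5.1. If the non-dominant hand were immersed for the heat sequence, a right-handed patient would have the left hand in water and the left forearm heated: the same limb, though not the same skin.
- **Staff could notice and adapt.** They could, but an unwritten adaptation would vary between patients and visits and leave no record of which limb was used.

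The heat-evoked potential text in Section 4.2.4, "Contact heat stimuli were delivered to the right, dominant proximal volar forearm", might be read as further support, or as implying that only right-handed patients enter. It is neither. It describes a different test with no cold immersion and is not an eligibility rule. It is a separate minor wording point.

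**Conclusion.** The point holds as a procedural defect of limited reach. Followed exactly, Section 4.2.5.1 puts both stimuli on the same forearm in every left-handed patient and in no right-handed patient. In the former, the post-immersion heat rating may mix local cooling with central modulation and is not comparable with the rest of the sample. About 4 to 10 of 70 patients are affected, assuming 5% to 15% left-handed.

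The consequence falls on one secondary mechanistic measure. Individual values, single-visit comparisons and EEG correlations are distorted; between-arm comparisons of change mainly gain noise. The documents do not establish bias in the treatment comparison, and the size of the cooling effect cannot be derived from them. The primary VAS endpoint (Section 4.1) and the sample size (Section 6.1.2.1) are unaffected.

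The correction is worth making before testing starts. Later analysis could at best set these patients aside, and only if handedness and the limb used had been recorded.

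**What to change.** 1. In Section 4.2.5.1, replace *left forearm* with *the forearm contralateral to the immersed arm*. Worded this way, the rule is right whichever limb is immersed and does not presume the answer to item 3.
2. Record handedness and the limb used for each stimulus, and use the same limbs at every evaluation.
3. Reconcile the two cold immersions: non-dominant hand at 10 degrees in Section 4.2.5, dominant arm at 12°C in Section 4.2.5.1. State which applies to which test.
4. Separately, tidy the wording in Section 4.2.4 that treats right and dominant as the same.

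The cost is a few words in the test procedure and one recorded item for handedness and limb, with no extra test, visit or equipment.
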